## Abstract

**Background:**

The Medical Research Council (MRC) ORACLE trial evaluated the use of co-amoxiclav 375 mg and/or erythromycin 250 mg in women presenting with preterm rupture of membranes (PROM) ORACLE I or in spontaneous preterm labour (SPL) ORACLE II using a factorial design. The results showed that for women with a singleton baby with PROM the prescription of erythromycin is associated with improvements in short term neonatal outcomes, although co-amoxiclav is associated with prolongation of pregnancy, a significantly higher rate of neonatal necrotising enterocolitis was found in these babies. Prescription of erythromycin is now established practice for women with PROM. For women with SPL antibiotics demonstrated no improvements in short term neonatal outcomes and are not recommended treatment. There is evidence that both these conditions are associated with subclinical infection so perinatal antibiotic administration may reduce the risk of later disabilities, including cerebral palsy, although the risk may be increased through exposure to inflammatory cytokines, so assessment of longer term functional and educational outcomes is appropriate.

**Methods:**

The MRC ORACLE Children's Study will follow up UK children at age 7 years born to 4809 women with PROM and the 4266 women with SPL enrolled in the earlier ORACLE trials. We will use a parental questionnaire including validated tools to assess disability and behaviour. We will collect the frequency of specific medical conditions: cerebral palsy, epilepsy, respiratory illness including asthma, diabetes, admission to hospital in last year and other diseases, as reported by parents.

National standard test results will be collected to assess educational attainment at Key Stage 1 for children in England.

**Discussion:**

This study is designed to investigate whether or not peripartum antibiotics improve health and disability for children at 7 years of age.

**Trial registration:**

The ORACLE Trial and Children Study is registered in the Current Controlled Trials registry. ISCRTN 52995660

## Background & Rationale

The sequaelae of preterm birth pose a significant public health problem. Children born before 37 weeks gestational age are at increasing risk of major disabilities, such as cerebral palsy, with decreasing gestation [1]. Furthermore, of the preterm children without disability, many will have important behavioural and educational difficulties. The ORACLE Children Study presents a unique opportunity to determine if a simple, inexpensive intervention reduces the long term sequaelae of preterm birth with benefit for individuals and their families.

The ORACLE trial evaluated the prescription of Co-amoxiclav 375 mg and/or erythromycin 250 mg to women either with PROM [2] or in SPL [3]. The trial reported that erythromycin did improve the composite primary outcome (death or major cerebral abnormality on ultrasound prior to discharge or chronic lung disease defined as needing oxygen therapy at 36/40 post conceptual age) in singleton babies born to women after PROM. The prescription of Erythromycin was also associated with improvement in other significant outcomes such as prolongation of pregnancy, reduction in the need for neonatal ventilation, oxygenation and treatment with surfactant, a decrease in oxygen dependence at 28 days of age or older, and fewer positive neonatal blood cultures. Although Co-amoxiclav was associated with prolongation of pregnancy, a significantly higher incidence of neonatal necrotising enterocolitis was found in these babies. In the group of women with SPL the use of neither Co-amoxiclav nor erythromycin were associated with any improvement in neonatal morbidity or mortality.

Following the ORACLE trial antibiotic treatment for preterm, prelabour rupture of the membranes (PROM) may become standard practice and so there will never be another opportunity to undertake this study and provide unbiased and reliable evidence on this subject.

There is increasing evidence that, in addition to preterm birth, perinatal infection is an independent antecedent of other disability, particularly cerebral palsy and chronic lung disease. Therefore, perinatal administration of antibiotics could prevent neurological and respiratory disability by two mechanisms, either by prolonging pregnancy and/or by eliminating infection. In contrast however, it is possible that prolongation of pregnancy may increase rather than decrease the risk of disability by continuing fetal exposure to inflammatory cytokines, which have also been implicated in the genesis of neurological damage [4] and chronic lung disease [5]. Some clinical evidence to support this possibility comes from two observational studies of neurodevelopmental outcome in preterm infants born after PROM which showed a higher risk of cerebral palsy or neurological impairment compared with gestation matched controls [6,7]. In addition, duration of membrane rupture had a direct relationship with the risk of neurological impairment [7].

The cerebral and respiratory benefits reported with erythromycin in women with PROM in the ORACLE trial may have been secondary to (a) prolongation of pregnancy and (b) a reduction of the effects of fetal and neonatal lung infection or inflammation. Supportive evidence for the latter comes from broncho-alveolar lavage fluid studies. Studies of the constituents of broncho alveolar lavage fluid have shown that infants who develop chronic lung disease have higher concentrations of neutrophils [8], proinflammatory cytokines[9,10] and proxy markers of neutrophil recruitment, than those who recover from respiratory distress syndrome[9,11]. There is also evidence that intrauterine lung inflammation is implicated in the genesis of chronic lung disease, since high concentrations of the potent profibrotic agent, transforming growth factor, have been described in the first broncho-alveolar lavage fluid after birth of infants who go on to develop chronic lung disease [5,12]. The MRC ORACLE Children Study provides a unique opportunity to determine whether the reductions in chronic lung disease found at discharge from hospital in the erythromycin group are reflected in a decreased incidence of respiratory disease and the need for therapy at 7 years of age.

Follow-up of the infants of women who presented with SPL is important, even in the absence of an apparent effect of antibiotics from ORACLE II [3] on short term morbidity. Many clinicians and researchers are convinced from observational evidence that a substantial proportion of SPL is caused by sub-clinical infection [13]. If this evidence is indeed correct then differences in childhood neurodevelopment and respiratory function could be detected between children born to women randomised to antibiotics compared with those randomised to placebo even though crude measures of early neurological damage or respiratory disease were no different between the groups during the perinatal period.

## Methods/Design

ORACLE was a double blind randomised controlled factorial design trial which evaluated whether giving broad spectrum antibiotics to women in SPL or with PROM improved neonatal mortality and morbidity.

Women were randomised to receive antibiotics and matching placebos 4 times daily for 10 days or until delivery, whichever was sooner. ORACLE tested Co-amoxiclav 375 mg and erythromycin 250 mg singularly and in combination.

This phase of the study – the MRC ORACLE Children Study – will follow-up children of women randomised to ORACLE at 7 years of age to determine whether antibiotics have effects on their development, educational attainment, and the risk of conditions such as cerebral palsy and respiratory illness. The MRC ORACLE Children Study will include the 8942 children born to those women randomised in the UK.

### Primary & secondary outcomes

The primary outcome is:

1) the overall level of disability (severe, moderate, mild, none) derived from the Multi-Attribute Health Status (MAHS) classification system.

The secondary outcomes are:

1) number of children with 3 or more abnormal attributes derived from the MAHS classification system

2) degree of function (severe, moderate, mild, none) within the 9 domains of vision, hearing, speech, ambulation, dexterity, emotions, cognition, pain and self care.

3) behaviour (Goodman's strengths and difficulties questionnaire).

4) educational achievement in reading, mathematics and writing at Key Stage 1. Data on both levels and raw scores will be collected.

5) incidence of specific medical conditions:

• cerebral palsy

• epilepsy

• respiratory illness including asthma

• diabetes

• admission to hospital in last year

• other diseases

• death – from trial entry to aged 7 years

- from initial discharge from hospital to aged 7 years

• covariates – family demographic information (housing status, ethnic group, smoking practice) will be collected.

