### Inclusion/exclusion criteria

#### Inclusions

• surviving children of mothers recruited to the ORACLE trial

• child resident in UK

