#### Exclusions

• recruited outside UK

• adopted or fostered children and children who have emigrated

Children who have been adopted or fostered will not be followed-up to avoid potential distress to parents and child. Children born in Scotland, Northern Ireland or Wales have different National Tests to England and therefore will not have data collected to assess educational achievement.

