### Estimated power of study

A total of 8942 babies survived until the end of data collection in England, Scotland, Wales and Northern Ireland. Of these, 4521 were in the SPL group and 4421 were in the PROM group. Not all of these babies will have survived until age 7 years; assuming an 85% response rate to a parental questionnaire, 3843 responses can be expected from the SPL group and 3758 from the PROM group (7601 in total).

Table 1 demonstrates the differences detectable between any two intervention groups for the listed primary measure (e.g. erythromycin vs. erythromycin-placebo) in each of the specified sub-groups (SPL and PROM). The estimates of prevalence of disability are based on data derived using the same instrument (MAHS Mark II) [14] on extremely low birth weight (ELBW) babies compared with a reference group of normal birth weight babies. As the majority of ELBW babies are born less than 28 weeks gestation they will have a higher prevalence of disability than the children included in the MRC ORACLE Children Study. For the measure of '3 or more attributes' affected, an incidence of 28% occurred in the ELBW group compared with 2% in the reference group. As the gestational age of the ORACLE population of children is between these extremes a conservative disability estimate of 5% has been taken as the principal estimate and sensitivity to variation of this value of the power of the study to detect differences is explored in the table. By ranking children into groups by their degree of disability (the number of attributes affected) the power of the study to demonstrate smaller differences will be increased by using tests for trends.

**Table 1 T1:** For each sub-group (PROM or SPL), a response from 3700 babies will allow the following differences to be detected with 80% power:

**Outcome**	Incidence in erythromycin group	Incidence in erythromycin placebo group	Relative risk reduction
**'3 or more attributes affected'**	**3.1%**	**5%**	**38%**
	5.6%	8%	30%
	1.5%	3%	50%

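### The single survivor-based eligibility list and the mislabelled base of 8942 do not fit the outcome of death from trial entry; the mortality outcomes need their own stated population

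*Protocol article*

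**What the plan says.** **Outcomes.** Under Primary & secondary outcomes, the Protocol article lists two mortality measures with different starting points: "death – from trial entry to aged 7 years" and "from initial discharge from hospital to aged 7 years".

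**Eligibility.** There is one list for the whole study. Inclusions are "surviving children of mothers recruited to the ORACLE trial" and "child resident in UK". Exclusions include "adopted or fostered children and children who have emigrated". For adopted and fostered children the reason given is to spare parents and child distress. No other population is stated for death.

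**The base.** Methods/Design says: "The MRC ORACLE Children Study will include the 8942 children born to those women randomised in the UK". Estimated power of study says: "A total of 8942 babies survived until the end of data collection in England, Scotland, Wales and Northern Ireland". The latter section adds that some of these babies will have died before age 7.

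**Sources of deaths.** Background & Rationale names death as a component of the parent trial's composite primary outcome. Data collection says ONS tracing will report deaths after hospital discharge, with quarterly listings of deaths and embarkations. Deaths are to be classified by cause (Death categorisations). The Analyses plan says methods for secondary outcomes will be adapted for survival measures.

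**The concern.** A mortality outcome that starts at trial entry belongs to every baby of every randomised woman in the comparison. The stated list admits survivors only, and the stated base has already lost the early deaths. Either one conditions a from-randomisation comparison on an event that happens after randomisation.

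Two consequences follow if the text is applied as written. First, the two mortality outcomes nearly collapse into one, since only late deaths remain in both, although the article plainly means them to differ. Second, the perinatal and neonatal period drops out of a result labelled as running from trial entry. Background & Rationale reports that in this period erythromycin improved a composite containing death, in singletons born after PROM. The article does not say whether death itself differed, but the period should not disappear without notice.

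**Working it through.** **Step 1. Reproduce the stated base (Estimated power of study).**
- 4521 (SPL) + 4421 (PROM) = 8942.
- Expected responses at 85%: 0.85 × 4521 = 3842.85, or 3843; 0.85 × 4421 = 3757.85, or 3758; total 7601.

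The figures agree with the article. The count of 8942 is therefore the survivor count, and Methods/Design attaches the same number to children born. Both descriptions can be true only if no baby died before ORACLE data collection ended, yet death was a component of the parent trial's primary outcome.

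**Step 2. Write the required denominator.** Let
- E = deaths from trial entry to the end of ORACLE data collection,
- U = babies whose status was unknown at that point,
- L = deaths among the 8942 from then to age 7,
- N = all babies of UK-randomised women.

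Then N = 8942 + E + U, and death from trial entry needs E + L as its numerator. The article gives none of N, E, U or L.

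**Step 3. Compare the possible readings.**
- *Eligibility list taken literally (surviving children only):* no events.
- *Base of 8942:* L deaths in 8942. E is absent from both numerator and denominator.
- *All babies of UK-randomised women:* E + L deaths, with N as the base. Only this reading matches the outcome's stated start. No sentence in the article sets it as the population.

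**Step 4. Size of the loss.** The share of known deaths outside the base is E / (E + L). For illustration only, assume later mortality between 0.2% and 5% of the 8942:
- 0.002 × 8942 = 18 deaths;
- 0.01 × 8942 = 89 deaths;
- 0.05 × 8942 = 447 deaths.

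The share passes one half only if E exceeds L. With E not given, the share cannot be stated.

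**Step 5. Can the number of women stand in for births?** The Abstract gives 4809 women with PROM and 4266 with SPL. In SPL there are more survivors than women (4521 − 4266 = 255), through multiple births, so the subtraction tells nothing about deaths. In PROM there are fewer survivors than women, but the Abstract does not clearly say that all 4809 were recruited in the UK, and the exclusions allow for recruitment elsewhere. The gap could include non-UK women or babies with unknown status as well as deaths.

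**Step 6. Do the exclusions fit a mortality outcome?** The distress reason concerns follow-up contact with families. Deaths come from ONS without such contact, so the reason does not carry over. Emigrated children need not be dropped either, because the ONS listings report embarkations and follow-up can be censored there.

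**The case against.** The strongest reply is that the survivor-only reading is the least plausible one. Listing two windows would be pointless if only survivors counted. Early deaths belong to the parent trial's outcome, later deaths come from ONS, and a cause-of-death classification is ready. The article already varies its population by outcome: education data are limited to England, and anonymised test levels cover all children in each treatment group, beyond those with parental consent. Analysis sets by outcome are also something that a condensed article may leave to a fuller document.

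Much of this stands. A reader might infer that death from trial entry cannot be measured at all. The article does not support that: the difficulty exists only inside the stated population, and the sources named in Background & Rationale and Data collection together can cover the whole window. A reader might also infer, by setting the PROM women against the PROM survivors, that most deaths fall outside the 8942. That is not supported either, for the reasons in steps 4 and 5 of the working.

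What the reply does not remove is the text itself. The eligibility list is not limited to questionnaire outcomes, nothing says that parent-trial deaths will be joined to the ONS deaths, and 8942 is described in two incompatible ways. Those are statements that conflict, which goes beyond detail left for later.

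**Conclusion.** The point holds as a contradiction about population. The eligibility list conflicts with the outcome of death from trial entry, and 8942 is mislabelled in Methods/Design and cannot be that outcome's denominator. It is certain that all deaths before the end of ORACLE data collection lie outside the 8942; how large a share they form cannot be derived from the article.

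The second window needs care too. The article does not date the end of data collection relative to discharge, so 8942 should not be assumed equal to the number discharged alive.

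The reach is limited to the secondary mortality outcomes. The primary disability outcome is unaffected, and so are the expected 7601 responses and Table 1, which rest on disability and not on death. The conclusion assumes that death from trial entry means what it says: every baby of a UK-randomised woman, counted from randomisation.

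**What to change.** State the population by outcome.

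- **Death from trial entry:** all babies of UK-randomised women, by allocated group. Join parent-trial deaths to ONS deaths, keep adopted and fostered children, and censor emigrated children at embarkation. Say explicitly how stillbirths are counted, since the window opens before birth.
- **Death from initial discharge:** all babies discharged alive, with the same treatment of adopted, fostered and emigrated children.
- **Outcomes that need contact with families:** the present inclusion and exclusion list, expressly limited to these.
- **Methods/Design:** describe the 8942 as children alive at the end of ORACLE data collection, and give the number of babies at randomisation by PROM/SPL and allocated group.

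The cost is a few sentences of wording and one merge of parent-trial outcomes with ONS listings that the study already plans to receive. It needs no new contact with families and no change to the sample size.

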### Inclusion/exclusion criteria

#### Inclusions

• surviving children of mothers recruited to the ORACLE trial

• child resident in UK

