### Postal parent-report questionnaire

A parental questionnaire will be administered to determine the level of disability (severe, moderate, mild, none). This is based on the Multi-Attribute Health Status (MAHS) Mark II and III [14] classification system developed and widely tested by the Departments of Paediatrics and Clinical Epidemiology and Biostatistics of McMaster University, Canada. The additional domain of behaviour is being assessed using the strengths and difficulties questionnaire developed and validated by Robert Goodman [15]. Additional questions will assess the other health related outcomes. Deaths will be categorised hierarchically using the system below developed by PMG and with the advice of [name], Consultant Pathologist, John Radcliffe Hospital, Oxford

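### The primary disability comparison is confined to children who survive, and no stated analysis combines death with disability, so it could be biased if an antibiotic changed survival, chiefly in the PROM stratum

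*Protocol article*

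**What the plan says.** Under Inclusions, the eligible population is "surviving children of mothers recruited to the ORACLE trial". Under Primary & secondary outcomes, the primary outcome is "the overall level of disability (severe, moderate, mild, none) derived from the Multi-Attribute Health Status (MAHS) classification system". It comes from a parental questionnaire (section Postal parent-report questionnaire), so it exists only for living children.

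Death is a separate item within the fifth secondary outcome: "death – from trial entry to aged 7 years", and again from initial hospital discharge to age 7. Deaths are traced through ONS (Data collection) and classified by cause (Death categorisations).

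The Analyses plan fits logistic models for disability prevalence by allocated group. It names four kinds of sensitivity analysis: modelling the level of disability, risk differences, multiple births, and covariate adjustment. None of them brings in the children who died.

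On earlier results, Background & Rationale says that "erythromycin did improve the composite primary outcome (death or major cerebral abnormality on ultrasound prior to discharge" or chronic lung disease), and it limits this to the effect "in singleton babies born to women after PROM". It also reports more necrotising enterocolitis with co-amoxiclav. For SPL it says that "the use of neither Co-amoxiclav nor erythromycin were associated with any improvement in neonatal morbidity or mortality".

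**The concern.** Randomisation protects a comparison of all babies of randomised women. It does not protect a comparison of those still alive at 7 if treatment influenced who survived. If an antibiotic kept alive some infants who would otherwise have died, and those infants carry more disability than average, they enter the treated arm's disability rate while their counterparts in the control arm are absent. The treated arm then looks worse than it should. If an antibiotic increased deaths among fragile infants, the selection would run the other way and flatter it.

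The article's own rationale gives this added weight. It puts forward the possibility that prolonging pregnancy raises disability through exposure to inflammatory cytokines. Apparent harm among survivors is what that hypothesis predicts, and it is also what selective survival would produce. Disability prevalence among survivors cannot tell the two apart. Reporting deaths separately would reveal a survival difference but would not correct the disability contrast.

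**Working it through.** **1. The plan's own figures.** The principal row of Table 1 is 3.1% v 5% with 80% power from 3700 responses per stratum. Alpha is not stated. Assuming two-sided 0.05 and 1850 v 1850 at the factorial margin, power is 83.5% without continuity correction and 81.3% with it, so the row reproduces with the correction. The expected responses also reproduce: 0.85 × 4521 = 3843, 0.85 × 4421 = 3758, 0.85 × 8942 = 7601.

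The 5% and 3.1% refer to three or more affected attributes, which the outcome list makes secondary. They serve here because they are the only disability rates the article plans on.

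**2. Inputs for the illustration.**
- From the article: control disability 5%; treated rate 3.1% if the planned effect is true; 28% in the ELBW reference data as one possible rate among extra survivors.
- Assumed, because the article gives no mortality by arm: control mortality m = 3–10%; deaths averted d = 0.5–2 per 100 babies; disability among the extra survivors q = 10–50%.
- Also assumed: treatment averts deaths but causes none.

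**3. Formula.** With S0 = 1 − m and p the treated disability rate in children who would survive under either allocation:

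observed treated rate = (S0 × p + d × q) / (S0 + d)

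**4. No true effect on disability (p = 5%).**
- Low end (m = 3%, d = 0.5, q = 10%): (0.97 × 0.05 + 0.005 × 0.10) / 0.975 = 5.03%.
- Middle (m = 6%, d = 1, q = 28%): (0.94 × 0.05 + 0.01 × 0.28) / 0.95 = 5.24%.
- High end (m = 10%, d = 2, q = 50%): (0.90 × 0.05 + 0.02 × 0.50) / 0.92 = 5.98%.

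Against the 1.9-point difference in Table 1 (5 − 3.1), the apparent harm is 0.03/1.9 ≈ 2%, 0.24/1.9 ≈ 13% and 0.98/1.9 ≈ 52%.

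**5. Planned effect true (p = 3.1%).** Power is continuity-corrected, with 1850 per arm.

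| m | d per 100 | q | Observed treated rate | Relative reduction | Power |
|---|---|---|---|---|---|
| none averted | 0 | – | 3.10% | 38% | 81% |
| 3% | 0.5 | 10% | 3.14% | 37% | 80% |
| 6% | 1 | 28% | 3.36% | 33% | 67% |
| 6% | 2 | 28% | 3.62% | 28% | 51% |
| 10% | 2 | 50% | 4.12% | 18% | 23% |

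The result depends on d and q and hardly on m. With d = 0, or q equal to the 5% background rate, the bias in the null case is nil.

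**6. What a combined outcome would show.** Take the middle null case. Death or disability on all babies is 0.06 + 0.94 × 0.05 = 10.7% in controls and 0.05 + 0.94 × 0.05 + 0.01 × 0.28 = 9.98% with treatment. The survivor comparison moves against the treatment (5% to 5.24%), while the combined outcome moves in its favour.

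**7. Why non-responders cannot simply be dropped.** Death is traced through ONS, while disability status is expected for only 85% of survivors. At 6% mortality, a complete-case composite would show deaths as 6 / (6 + 0.85 × 94) = 6 / 85.9 = 7.0%. Among the 8942, expected non-response is 8942 − 7601 = 1341 children.

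**The case against.** The strongest reply is that the article does not show that survival differed. The improved composite also contains cerebral abnormality and chronic lung disease, and the other erythromycin benefits listed are prolongation of pregnancy and measures of morbidity. The benefit is stated only for PROM singletons. SPL, with 4521 of the 8942 children, is reported as showing no improvement in mortality. All of this stands. A reader might infer that erythromycin saved lives and that the primary comparison is therefore biased across the study; the article supports neither step.

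A second reply is that death is already handled: two observation periods, tracing, cause classification, and secondary analyses by allocation adapted for survival measures. This also largely stands. A reader might see a clash between the survivor inclusion criterion and a death outcome counted from trial entry. But counting from trial entry already implies all babies of randomised women, and the criterion reads naturally as saying who is sent a questionnaire. What remains is that separate reporting leaves the primary contrast uncorrected, and nothing requires the two to be read together.

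A third reply is that a questionnaire needs a living child, that disability at 7 is a legitimate question, and that the list of sensitivity analyses is open-ended, so an unshown analysis plan may add one. The survivor analysis is indeed legitimate and need not be replaced. The request is for an addition; it does not allege a contradiction. It is still worth making, because the article itself fixes population, outcome and model and names its sensitivity analyses, and none deals with death.

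**Conclusion.** The point holds as a possible bias. The primary comparison is conditioned on survival after randomisation, and no stated analysis combines death with disability. It matters mainly for PROM, where the reported composite benefit of erythromycin and the excess of necrotising enterocolitis with co-amoxiclav make a survival difference in either direction plausible. For SPL the article gives little reason to expect one.

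The size cannot be determined from the document. Under the assumed ranges, a null 5% would be seen as about 5.03–5.98%, and the planned 38% reduction as 37% down to 18%. Only the combination of 2 deaths averted per 100 and a high disability rate among the extra survivors brings the bias to about half of the planned difference. At half a death averted per 100 and 10% disability it is negligible. The supporting analysis should be added; the primary analysis need not be abandoned.

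**What to change.** Keep the survivor-only primary analysis. Add to the sensitivity analyses in the Analyses plan a supporting analysis by allocated group, separately within PROM and within SPL, on all babies of UK-randomised women:

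- an ordinal outcome with death from trial entry as the worst category, above severe, moderate, mild and no disability;
- a binary outcome of death or disability, with the disability cut fixed in advance;
- death and disability shown separately beside the composite;
- missing disability status in survivors handled by multiple imputation or response weighting, not by dropping non-responders;
- a statement that the survivor-only result will be interpreted alongside this analysis.

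The cost is modest. Later deaths come from ONS, and deaths before discharge were part of the parent trial's primary outcome, so no new data collection is needed. The missing-data step adds some analysis work. The main drawback is that a composite mixes outcomes of different weight, and deaths that treatment does not affect dilute a true effect on disability. Both are reasons to use it as support, with its components shown.
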